### **11.3 Sample size**

The study is powered for the supposed change caused by the intervention in global left ventricular ejection fraction between the intervention group and placebo group at 4 months after hospitalization. This trial is primarily intended as a proof of concept study, and therefore not powered for a mortality benefit, but for the surrogate endpoint difference in left ventricular ejection fraction measured with CMR imaging 4 months after primary PCI. Van der Vleuten et al (8) demonstrated that a decrease of 5% in LVEF after STEMI leads to a HR of 1.44 for mortality at 1 year follow-up. The recently published HEBE III trial assumed a 3% change in LVEF to be clinical relevant

and to be feasible. Therefore a difference of 3% in LVEF is a relevant primary endpoint. With 141 patients in each study group, the study has 80% power to detect a 3% difference in change in ejection fraction between active treatment and control, assuming a 2-sided  $\alpha$  of .05 for the change in left ventricular ejection fraction.

### 11.3.1 Sample size calculation

The following formula was used to assess the sample size (N) per group. The entire sample size will therefore be 2N.

$$N = (A + B)^2 \times 2 (\sigma^2 / \delta^2)$$

|            |                                            |      |
|------------|--------------------------------------------|------|
| N =        | sample size of 1 group (Total sample = 2N) | ?    |
| A =        | significance level (5%=1,96)               | 1,96 |
| B =        | power (80%=0,84)                           | 0,84 |
| $\sigma$ = | expected standard deviation                | 9    |
| $\delta$ = | delta (clinical relevant difference)       | 3    |

This results in the following calculation:

$$N = (1,96 + 0,84)^2 \times 2 (9^2 / 3^2)$$

$$N = (2,8)^2 \times 18$$

$$N = 7,84 \times 18$$

$$N = 141$$

Sample size (2N) = 282

We assumed that in 12% of patients a primary endpoint observation would not be obtained. However, actual rates of patients not undergoing cardiac MRI (primary endpoint) differ from that assumption. Actual rates are close to 26%, therefore we require an increase to 380 patients , assuming that in 26% of patients no primary efficacy measurement will be obtained.

## **12. ETHICAL CONSIDERATIONS**

### **12.1 Regulation statement**

The study will be conducted according to the principles of the Declaration of Helsinki (2008, Seoul) and in accordance with the Medical Research Involving Human Subjects Act (WMO).

### **12.2 Informed consent**

The purpose and details of the study are explained to all patients by a cardiologist and their verbal consent will be obtained prior to participation in the study by a cardiologist. Patients are enrolled in an emergency situation, and therefore consent is given verbally in the presence of an independent witness. Because of the acute situation, there is limited time for the patient to consider participation. If the patient expresses any doubt considering participation, the cardiologist will not enroll the patient. Written informed consent has to be given by the patient as soon as the clinical situation of the patient allows it.

The patient information letter and informed consent form is attached (see attachments).

### **12.3 Insurance**

The Onderlinge Waarborgmaatschappij Centramed, [name] (polis number 624.529.102) has a liability insurance which is in accordance with the legal requirements in the Netherlands (Article 7 of the WMO and the Measure regarding Compulsory Insurance for Clinical Research in Humans of June 23th, 2003) This insurance provides cover for damage to research subjects through injury or death caused by the study procedure:

1. €450.000,- (i.e. four hundred and fifty thousand Euro) for death or injury for each subject who participates in the Research caused by study procedure;
2. €3.500.000 (i.e. three million five hundred thousand Euro) for death or injury for all subjects who participate in the Research caused by study procedure;

3. €5.000.000 (i.e. five million Euro) for the total damage incurred by the organization for all damage disclosed by scientific research.

The insurance applies to the damage that becomes apparent during the study or within 4 years after the end of the study.

#### **12.4 Incentives**

Patients will not receive any special incentives, compensation or treatment through participation in the study, with the exception of travel expenses if applicable for a specific study subject.

## **13. ADMINISTRATIVE ASPECTS**

### **13.1 Handling and storage of data and documents**

For each randomized patient, a electronic Case Record Form (eCRF) for data recording is provided. CRFs are coded with a study code combined with a patient number, which will be used in ascending numerical order. The Oracle Clinical electronic Case Record Form will be used for the GIPS-III trial. All data will be recorded in a dedicated database.

The investigator will ensure that patient anonymity is maintained according to the Personal Data Protection Act (WBP). On CRFs or other documents, patients are not identified by their names but by the CRF code. Only the investigators and co-investigators will have access to the CRF code. The coordinating investigator will keep a separate log of patient codes, names and addresses.

### **13.2 Subsidizing party**

This trial is subsidized by the Van Buchem Stichting and by grant 95103007 by the ZonMw, the Netherlands Organization for Health Research and Development, The Hague, the Netherlands.

### **13.3 Amendments**

All substantial amendments will be sent for approval to the METC that gave a favorable opinion. A substantial amendment is defined as an amendment to the terms of the METC application, or to the protocol or any other supporting documentation, that is likely to affect to a significant degree:

- the safety or physical or mental integrity of the subjects of the trial;
- the scientific value of the trial;
- the conduct or management of the trial;
- the quality or safety of any intervention used in the trial.

Non-substantial amendments will not be notified to the accredited METC, but will be recorded and filed by the sponsor.

**13.4 Progress report**

Information will be provided to the METC once a year on the date of inclusion of the first subject, numbers of subjects included and numbers of subjects that have completed the trial, serious adverse events/ serious adverse reactions, other problems, and amendments.

**13.5 End of study report**

The investigator will notify the accredited METC of the end of the study within a period of 8 weeks.

The end of the study is defined as the last patient's last visit.

Within one year after the end of the study, the investigators will submit a final study report with the results of the study, including any publications/abstracts of the study, to the accredited METC.

**13.6 Publication policy**

Investigators will be encouraged to publish and present the results of the study. All publications will be reviewed and approved by the Executive Committee. The Executive Committee consists of the following members: [name] (MD, PhD), [name] (MD) and [name] (MD, PhD).

Investigators and the Executive Committee will publish the study results in compliance with the CCMO publication policy.

## 14.APPENDIX

### 14.1. NYHA heart failure classification

- Class I: patients with no limitation of activities; they suffer no symptoms from ordinary activities.
- Class II: patients with slight, mild limitation of activity; they are comfortable with rest or with mild exertion.
- Class III: patients with marked limitations of activity; they are comfortable only at rest.
- Class IV: patients who should be at complete rest, confined to bed or chair; any physical activity brings on discomfort and symptoms occur at rest.

### 14.2 Current guidelines on diagnosis of diabetes and prediabetes

#### Diabetes Mellitus

- HbA1c  $\geq 6.5\%$  or;
- Fasting glucose  $\geq 7.0$  mmol/L or;
- OGTT glucose  $\geq 11.1$  mmol/L.  
(measured at 120 minutes post glucose drink)

#### Prediabetes

- HbA1c 5.7-6.4% or
- Fasting glucose 5.6-6.9 mmol/L (venous) (ADA) : Impaired fasting glucose (IFG);
- OGTT glucose 7.9-11.0 mmol/L (venous), WHO): Impaired glucose tolerance (IGT).  
(measured at 120 minutes post glucose drink)

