## 1. RATIONALE

Patients with impaired glucose tolerance or diabetes have a 2 to 4 fold higher risk of developing cardiovascular disease (CVD) (1). In patients with diabetes the prevalence of myocardial infarction and heart failure is higher than in individuals without diabetes. Cardiac death is the main cause of mortality in patients with diabetes (2). After diagnostic testing 25 to 45% of patients with an acute coronary syndrome have diabetes, whereas the prevalence of diabetes in the general population varies between 10 to 15% (3). Up to 65% of patients with an acute coronary syndrome have diabetes or metabolic disturbances (3).

Both after primary percutaneous coronary interventions (PCI) and coronary artery bypass grafting (CABG), patients with diabetes have a higher risk of cardiac death (4;5) and worse left ventricular function (6). Comparing patients with newly detected type 2 diabetes to patients with previously established diabetes, both groups have comparable proportions of re-infarction, stroke, and long-term mortality following acute myocardial infarction (4). Subdividing cardiac death, the rate of sudden cardiac death in patients with diabetes is comparable to patients without diabetes, whereas heart failure is the main cause of the attributive cardiac death in patients with diabetes (7).

In acute myocardial infarction, several therapies including early primary percutaneous coronary interventions and ACE-inhibitors aim to preserve ventricular function and thereby prevent the development of heart failure (3).

Patients with impaired left ventricular function after revascularization have worse prognosis (8). Patients with metabolic disturbances or diabetes are likely to develop heart failure (9;10). Moreover, increased admission glucose levels (11) and persistent hyperglycemia (12) are related to a higher

mortality in patients with acute MI, regardless of diabetic status. These elevated glucose levels are thought to reflect pre-existent impaired glucose tolerance or increased physical stress.

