### 2.2 Secondary objectives

Secondary study objectives include the investigation of the impact of metformin treatment on:

- the incidence of a cardiovascular event within 4 months and after long-term follow-up (all cause mortality, cardiovascular death, re-infarction, re-intervention (both re-PCI and CABG), stroke and combined endpoints) (see table 1);
- the incidence of hospitalization for heart failure within 4 months and after long-term follow-up;
- the prevalence of new onset diabetes and prediabetes as defined by the current guidelines ;
- laboratory parameters associated with improving outcome as assessed by glycometabolic state (e.g. fasting blood glucose, HbA1c, insulin, GLP-1, HOMA-IR), inflammatory state (e.g CRP, high-sensitivity CRP, TNF-alpha, IL-6), lipid and cholesterol spectrum (e.g. LDL, HDL, total cholesterol, triglycerides), advanced glycation endproducts (e.g AGEs), renal function (e.g hemoglobin, hematocrit, MDRD), and neurohormones (e.g NT-proBNP, plasma renin activity, aldosterone) and protein profiles (mRNA, DNA) before hospital discharge and at each outpatient clinic visit.
- Infarct size and TEI using LGE CMR imaging 4 months follow-up.
- Electrocardiographic determinants of myocardial perfusion (incidence of new Q waves, ST-segment resolution, persistent ST-deviation) during hospitalization and each outpatient clinic visit.
- systolic and diastolic function using echocardiographic parameters during hospitalization and at 4 months follow-up.
- Body Mass Index (BMI) before hospital discharge and at each outpatient clinic visit.

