| - Heart failure                   |                | A        |
| - chest pain                      |                | B        |
| ICD implantation                  | 6              |          |
| New onset diabetes                | 7              |          |
| Prediabetes                       | 8              |          |

Tabel 1: Clinical secondary endpoints.

A non-elective hospitalization (defined as an overnight stay, with different dates for admission and discharge) for clear symptoms of heart failure within 4 months and after long-term follow-up will be recorded. Furthermore, non-elective hospitalization (defined as an overnight stay, with different dates for admission and discharge) for chest pain will be recorded as an endpoint. Implantation of an internal cardiac defibrillator (ICD) will be recorded as an endpoint. Hospitalization for other reasons than heart failure or chest pain will not be recorded as an endpoint. Whenever a patient undergoes an elective PCI, CABG, or ICD implantation, or has a recurrent myocardial infarction or stroke, the patient is (likely to be) hospitalized. Therefore, in case of these events, the hospitalization itself will not be recorded as a separate endpoint. New onset diabetes and prediabetes, as defined by the guidelines (see Appendix 14.2) will be recorded as an endpoint. Whenever new onset diabetes is

diagnosed, patients will be treated by an endocrinologist at University Medical Center Groningen according to current guidelines. Treatment for diabetes will be additional to study treatment. Visits for treatment will be separate from study visits.

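### Endpoint 8 (prediabetes) counts a closed middle band separately from new onset diabetes, so an arm difference in it alone cannot be read as benefit or harm

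*Protocol*

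**What the plan says.** Table 1 in section 9.1.2 gives the two diagnoses their own classes: "New onset diabetes | 7" and "Prediabetes | 8". The text below the table makes both of them events: "New onset diabetes and prediabetes, as defined by the guidelines (see Appendix 14.2) will be recorded as an endpoint". Section 9.3.4.2 likewise treats a diagnosis of either as an endpoint. Section 2.2 names them together as a secondary objective: "the prevalence of new onset diabetes and prediabetes as defined by the current guidelines".

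Appendix 14.2 leaves diabetes open above (HbA1c from 6.5%, "Fasting glucose $\geq 7.0$ mmol/L or", OGTT from 11.1 mmol/L). It closes prediabetes at the top: HbA1c 5.7-6.4%, "Fasting glucose 5.6-6.9 mmol/L (venous) (ADA"), OGTT 7.9-11.0 mmol/L. Within each diagnosis the tests are alternatives, so one positive test is enough.

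The protocol gives no rule that ranks the two classes, and no endpoint defined as prediabetes or worse. Section 11.1 compares proportions with a chi-square or Fisher's exact test.

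**The concern.** Metformin lowers glucose. If it works, it moves some patients across the lower edge of the band into the normal range, and it keeps others below the upper edge who would otherwise have been diabetic. The first group lowers the count of endpoint 8 and the second raises it. A fall, a rise or no change in endpoint 8 is thus compatible with the same favourable shift in glycaemia.

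What is at stake is how one secondary result is read. A chi-square test on endpoint 8 alone could be reported as no effect on prediabetes, or even as a small excess on metformin, when prediabetes and diabetes taken together have become less frequent.

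There is also an overlap. A patient with fasting glucose 7.2 mmol/L and HbA1c 6.0% meets the diabetes definition on the first test and the prediabetes definition on the second. The text does not say which class counts.

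**Working it through.** **The plan's own figure.** The only calculated size is for LVEF (section 11.3.1): (1.96 + 0.84)² × 2 × 9²/3² = 7.84 × 18 = 141 per group, 282 in all. With 26% missing, 282/0.74 = 381, against 380 stated. It reproduces. It bears on this point only by giving 380/2 = 190 per arm. No figure is given for diabetes or prediabetes.

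**Sign of the effect.** Let A be the proportion with prediabetes or diabetes, D the proportion with diabetes, and B = A − D the band, with each patient in one category. Then ΔB = ΔA − ΔD. A downward shift makes both ΔA and ΔD negative, so ΔB = −|ΔA| + |ΔD|, which has no fixed sign. ΔA and ΔD each do.

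**Illustration for patients without known diabetes.** Assumed: control A = 40%, D = 10%, and a uniform downward shift of 0.3 SD on a normal scale.
- A: Φ(−0.253 − 0.3) = 29.0%, a change of −11.0 points.
- D: Φ(−1.282 − 0.3) = 5.7%, a change of −4.3 points.
- B: 30.0% to 23.3%, a change of −6.7 points (61% of −11.0).

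Power, two-sided 5%, n per arm, p̄ the mean of the two rates: Φ{[|p1 − p2| − 1.96 √(2p̄(1 − p̄)/n)] / √(p1(1 − p1)/n + p2(1 − p2)/n)}. With n = 190:
- Prediabetes or diabetes: (0.1100 − 0.0956)/0.0484 = 0.30, power 62%.
- Band: (0.0669 − 0.0889)/0.0452 = −0.49, power 31%.

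**Sensitivity to the assumptions.**

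| Control A / D | Shift | n per arm | Change in A | Change in band | Power A / band |
|---|---|---|---|---|---|
| 40% / 10% | 0.3 SD | 190 | −11.0 | −6.7 | 62% / 31% |
| 40% / 10% | 0.3 SD | 140 | −11.0 | −6.7 | 49% / 24% |
| 40% / 5% | 0.3 SD | 190 | −11.0 | −8.6 | 62% / 44% |
| 40% / 10% | 0.15 SD | 190 | −5.7 | −3.3 | 21% / 11% |

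The 140 per arm is 380 × 0.74/2, rounded, if tests are missing as often as CMR.

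**When it cancels or reverses.** Fasting glucose only, assumed normal with SD 0.7 mmol/L, shifted down by an assumed 0.3 mmol/L, band from 5.6 to 7.0:

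| Control mean | Inflow from diabetes | Outflow to normal | Net change in band | Share offset |
|---|---|---|---|---|
| 5.6 | 1.5 | 16.6 | −15.1 | 9% |
| 6.0 | 4.5 | 15.9 | −11.4 | 28% |
| 6.3 | 8.2 | 12.5 | −4.3 | 66% |
| 6.6 | 12.5 | 8.2 | +4.3 | over 100% |

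With SD from 0.5 to 1.0 the offset share is 1-31% at mean 5.6, 9-54% at 6.0 and 44-81% at 6.3. At 6.6 the sign is reversed throughout.

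**Using the effect that the protocol cites.** The Rationale quotes a 40% relative and 6-point absolute reduction in new diabetes, which implies 0.06/0.40 = 15% falling to 9%. That was over 1.8 years in people at risk, so it is illustrative here. Assume 40% prediabetes in controls, so A = 55%.
- A unchanged: band 55 − 9 = 46%, a change of +6.0.
- A falls by a relative 10% to 49.5%: band 40.5%, a change of +0.5 while A falls 5.5.
- A falls by a relative 20% to 44.0%: band 35.0%, a change of −5.0 while A falls 11.0.

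**The case against.** The strongest reply has four parts.

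First, the bands are guideline diagnostic classes, correctly presented as such. That stands. The difficulty lies only in using a capped class as a stand-alone event.

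Second, nothing is lost to the trial as a whole. Whatever enters the band from above appears in full as a fall in endpoint 7. Fasting glucose and HbA1c are measured repeatedly, and section 11.1 provides baseline-adjusted regression and GEE for such data. That also stands, and it limits the point to how endpoint 8 is read. The wording of section 2.2 could be taken as one pooled item, but Table 1 separates the two.

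Third, section 9.3.4.2 already sorts patients into normal, impaired regulation and newly detected diabetes, and ranking discordant tests is the sort of detail left to an analysis plan. The three-state classification is stated only for the hospital stay, not for the endpoints. The ranking of tests may well be settled elsewhere, but the list of separate endpoints and their cut-offs is fixed in the protocol itself.

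Fourth, a reader might infer that the treatment effect simply cancels, especially from the Rationale: "After diagnostic testing 25 to 45% of patients with an acute coronary syndrome have diabetes" and "Up to 65% of patients with an acute coronary syndrome have diabetes or metabolic disturbances". Taking 65% and 25% as control rates with the same 0.3 SD shift, the band falls 3.1 points against 11.6 for the combined category. With 65% and 45% it falls 0.1. The documents do not support that as the expected case. Those figures describe acute coronary syndrome patients in general, while section 5.3 excludes diabetes and section 9.3.4.2 excludes anyone with an established diagnosis or on glucose-lowering drugs. The rarer diabetes is among those enrolled, the smaller the dilution.

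**Conclusion.** The point holds as a matter of definition: endpoint 8 is not monotone in glycaemia, so a difference in it alone shows neither benefit nor harm. The dilution ranges from slight to complete or reversed, and the protocol gives no glycaemic distribution from which to say where this trial falls. In the closer illustration the band keeps 6.7 of 11.0 points and about half the power (31% against 62%). That rests on assumed control rates of 40% and 10%, an assumed 0.3 SD shift, normality, and 190 patients per arm with data. At half the shift neither definition has useful power (21% against 11%).

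The double classification of patients with discordant tests follows directly from the text and needs no assumption. Endpoint 7, the continuous glycaemic measures and the LVEF primary analysis are untouched. Severity is minor: one class among the secondary endpoints.

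**What to change.** Leave the diagnostic cut-offs in Appendix 14.2 and endpoint 7 as they are. State that each patient is assigned the worst category met on HbA1c, fasting glucose or OGTT. Then either analyse endpoint 8 as prediabetes or diabetes (at or above the lower cut-off on any of the three tests), or compare normal, prediabetes and diabetes between arms with one ordinal test. Report the prediabetes band descriptively beside it.

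The cost is a change of wording in Table 1 and section 9.1.2. All three tests are already planned, so no new data are needed. There is one drawback: the combined endpoint contains every endpoint 7 event, so the two overlap, and endpoint 8 must be relabelled because it is no longer prediabetes in the guideline sense.

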**16. ATTACHMENTS**
